## Abstract

**Introduction:**

Bipolar disorder (BD) is a common and debilitating mental illness that affects about 400 million people worldwide, decreasing their functionality and quality of life. Medication and psychotherapy are recommended for treatment of BD, while some evidence indicates that exercise could improve the clinical outcome of BD. This study aims to investigate whether exercise intervention could reduce the mood symptoms and inflammation level of BD.

**Methods:**

This is a longitudinal, interventional, randomized, and single-blind trial. We plan to recruit 94 patients diagnosed with BD in depression episode. Patients will be randomly assigned to treatment as usual + aerobic exercise group (intervention group) and treatment as usual (TAU) only group, at a ratio of 1:1. The intervention group will undergo 40-min aerobic exercise training twice a week for eight weeks. The primary outcome of this study is the mean change of Hamilton Depression Rating Scale 17 (HAMD 17) scores from baseline to week 8. The Young Manic Rating Scale (YMRS), Self-Rating Depression Scale (SDS), and Interleukin-6 (IL-6), Tumor necrosis factor-α (TNF-α) and C-reactive protein (CRP) levels will also be measured. The measurements will be performed at baseline, immediately after intervention and two months after intervention.

**Discussion:**

Aerobic exercise training + treatment is expected to bring more benefits to BD patients than TAU only. This trial might provide stronger evidence of physical exercise efficacy for BD treatment.

**Clinical trial registration:**

This study was approved by the Chinese Clinical Trial Registry (Registration Code: ChiCTR2200057159). Registered on 1 March 2022.

## Introduction

Bipolar disorder (BD) is a chronic, recurrent, psychiatric disorder characterized by alternating episodes of depression and mania/hypomania, affecting about 2.4% of the population worldwide across diverse cultures and ethnic groups (1), leading to substantial medical burden. Serious mental illness (SMI) includes BD, major depression disorder (MDD) and schizophrenia-spectrum disorders. BD patients have high rates of suicide, disability, and low social functioning, placing a significant burden on families and society (2). BD is also the seventeenth leading cause of disability worldwide (3).

Medication and psychotherapy are commonly used to treat BD (4), but their efficacy remains unsatisfactory. Compared to manic episodes, depression episodes in BD are more incapacitating, prolonged and frequent (5). Hence, mood stabilizers, antipsychotics, and antidepressants are often used as pharmacotherapy. Lithium is commonly used and found to be effective in some patients (6), but is also more likely to cause safety events compared to placebo (7). Additionally, there is significant controversy over the use of antidepressants (8–10), which may cause mania and the treatment for mania may rebound as depressive episodes (11). Although psychosocial treatments are effective for BD (6, 12), psychotherapy is not easily accessible and expensive. Therefore, the treatment for BD remains a huge challenge, especially in depression episodes (8–10).

In this context, exercise is recommended as an adjunctive therapy for BD. Exercise has been considered useful in major depression and schizophrenia, and is recommended by the European Psychiatric Association (EPA). Exercise is considered important for people with SMI, including schizophrenia-spectrum disorders, MDD and BD, because these patients typically engage in significantly more sedentary behavior and less physical activity (13, 14), which also puts them at higher risk of developing cardiovascular and metabolic diseases (13, 15, 16). Significant evidence supports the use of exercise interventions in the treatment of MDD (17) and schizophrenia-spectrum disorders. For example, exercise could improve mental and physical heath among general population, while physical activity could reduce recurrence, relieve depressive symptoms and improve cardiorespiratory fitness and quality of life for MDD patients (18–21). The EPA suggested moderate-vigorous intensity aerobic exercise 2–3 times per week for MDD and schizophrenia-spectrum disorders, which is similar to the recommendation of the American College of Sports Medicine (ACSM) for normal population (22).

However, current evidence is insufficient to include exercise as daily recommendation for BD population since exercise-based clinical trials in this population have been consistently poor. Previous systematic reviews concluded that although exercise treatment is promising for BD, existing studies have limitations (23–26).

For example, a pilot study found that individuals with BD who participated in 40-min walking group, five times a week for 24 months reported lower depression symptoms than those who did not, without a control group (27). Another pilot study found that lifestyle intervention including exercise program showed improvement in overall functioning assessed by The Longitudinal Interval Follow-Up Evaluation-Range of Impaired Functioning Tool, but no differences in mood symptoms between groups (28). A randomized controlled trial found that 30-h aerobic exercise intervention did not augment cognition compared to the control group (29). A recent randomized trial, examining effects of N-acetylcysteine for BD, found that patients with BD who engaged more physical activity may reduce more scores on the Bipolar Depression Rating Scale. Physical activity which could enhance mitochondrial may be a novel treatment for BD (30). The possible mechanism of exercise for treating BD includes augmenting the synthesis of monoamine neurotransmitters (30–34), neurotrophin types (35, 36), and anti-inflammation. Inflammation has been shown to decrease after aerobic exercise in the general population (37) and patients with depression (38–40). Also, increasing evidence indicates that inflammatory factors are potential biomarkers of BD in evaluating severity of BD mood symptoms. Recently, a large meta-analysis indicated that C-reactive protein (CRP) and Tumor necrosis factor- α (TNF-α) might be considered as “mood episode” markers of BD, while Interleukin-6 (IL-6) was speculated to be a trait marker of BD (41). The above-mentioned data implies that CRP, TNF-α, and IL-6 could be used to examine the exercise efficacy in BD treatment.

Several researches have documented the reduction of Brain-derived Neurotrophin (BDNF) among BD patients (42, 43). At the biological level, physical exercise increases the levels of neurotransmitters, cortisol, β-endorphins, and neurotrophins such as BDNF (44, 45). BDNF could enhance neuronal ATP production in several ways (46). Also, BDNF plays an important role in brain plasticity, neuron differences and survival, neuronal function and stimulates neurogenesis by activating TrkB. There are two forms of BDNF receptors: active TrkB-FL and inactiveTrkB-T1 (47). It has been shown that physical exercise increases the levels of neurotransmitters, cortisol, β –endorphins, and neurotrophins such as BDNF, through a PGC-1α/FNDS5 pathway (48). Thus, BDNF signaling system could play a role in the pathophysiology of BD (49).

The main hypothesis of this trial is that aerobic exercise is an effective therapy to improve depressive symptoms among bipolar depression patients.

## Method and analysis

### Study objective

The primary objective of this study is to assess whether 8-week aerobic exercise will improve depressive symptoms among BD patients compared to treatment as usual. The secondary objective is to explore the effect of aerobic exercise training on inflammatory biomarkers such as CRP, IL-6, and TNF-a, manic symptoms, and cardio-respiratory fitness compared to treatment as usual. The exploratory objective is to evaluate the effects of aerobic exercise on BDNF level, emotional symptoms, quality of life, and other physical parameters, 8 weeks after intervention. The results may provide evidence for exercise therapy benefits among BD patients.

### Study setting

This trial is a longitudinal, interventional, randomized, single-blind trial to be conducted at the First Affiliated Hospital of Chongqing Medical University, China. BD patients will be randomly divided into two groups: (1) Treatment as usual + aerobic exercise group (intervention group); (2) Treatment as usual group (control group).

The treatment as usual for participants in this study would be decided by a professional psychiatrist. Patients continue to be seen for medication visit every 2–4 weeks. There is no prohibition about medication changes during the trial. All pharmacotherapy including any changes in dose or medication will be recorded in detail.

### Eligibility criteria

The participants will be recruited from the Psychiatry Outpatient Department in the First Affiliated Hospital of Chongqing Medical University, China. Research assistants will use the Mini-International Neuropsychiatric Interview (MINI), a structured diagnostic interview, to confirm the diagnosis of DSM-5 bipolar disorder depression episode before inclusion.

#### Inclusion criteria

1.Aged 18–50 years old, female or male.2.A diagnosis of BD depression episode according to the Diagnostic and Statistical Manual of Mental Disorders-5 (DSM-5).3.The score of HAMD ≥ 17, the score of YRMS < 6.4.Adequate audiovisual skills to complete the necessary checks for the study.5.Willing to participate in this trial, with signed written informed consent.

#### Exclusion criteria

1.BMI ≥ 40 kg/m^2^.2.Systolic pressure ≥ 140 mmHg or diastolic pressure ≥ 90 mmHg.3.Perinatal or lactation period.4.Exercise time > 40 min per week over the last 6 months.5.Serious physical illness (such as heart disease, diabetes, hyperthyroidism, etc.).6.Infectious diseases, autoimmune diseases, use of anti-inflammatory drugs, cortisol hormones or antibiotics over the last 6 months.7.Severe suicidal ideation or attempt in last 30 days or need to be hospitalized immediately due to suicidal ideation, attempt, or behaviors.

### Outcomes

The primary outcome of this study is the HAMD 17 score mean change from baseline to week 8. Participants will be assessed with HAMD 17 at baseline and week 8. The secondary outcomes are the changes of CRP, TNF-α, and IL-6 from baseline to week 8.

### Participant timeline

Figure 1 shows a clear and concise timeline of the study visits, enrollment process, interventions, and assessments to be performed on participants.

**FIGURE 1 F1:**
[figure not shown]
Flow of precedure. TAU, Treatment as usual.

### Sample size

The sample size was calculated based on the primary hypothesis. To calculate the sample size, we reviewed some literature related to the main topic and used the PASS.15 software. Power was determined as 0.09 with α = 0.05. According to related study (50), the mean value among Chinese BD patients is 13, and standard deviation is 6. It was determined that permissible error was 1/3 of the mean value, δ = 4.3, population standard deviation σ = 6. It’s necessary to have 42 samples per group. According to similar study (51, 52), it’s possible to have 20% drop-out, and we won’t replace the subjects if participants drop out. So, it is necessary to have 53 patients per group (Supplementary material).

### Recruitment

Potential participants will be recruited from the Psychiatry Outpatient Department of the First Affiliated Hospital of Chongqing Medical University, China, which is one of the largest hospitals in southwest China. A post will be put in the Psychiatry Outpatient Department to advertise this trial and patients interested in the trial can contact us for information and participation. Researchers will also call potential participants to invite them to join the study. The recruitment will be conducted from March 2022 to December 2022 (Table 1).

**TABLE 1 T1:** Schedule of the enrollment, intervention, and assessments.

		Study period					
	
		Enrolment	Allocation	Post-allocation			
			
Time point		−t_1_	t_0_	t_1_ week 1	t_2_ week 4	t_3_ week 8	t_4_ month 4
Enrolment	Eligibility screen	×					
	Informed consent	×					
	Allocation		×				
Interventions	Exercise intervention			–	–	–	
Assessments	Sociodemographic variables		×				
	Physical parameters		×			×	×
	HMAD 17		×		×	×	×
	YMRS		×		×	×	×
	SDS		×		×	×	×
	Cardiorespiratory fitness		×			×	×
	Biological variables: CRP, TNF-α, IL-6, BDNF		×			×	×

#### Screening failures

Screening failures are defined as ineligible participants based on screening assessments. We will record the reason for screening failure, date of screening, and participant identification number.

#### Participant withdrawal or discontinuation

All participants will be free to quit the study for any reason at any time, and we will record reasons and date of dropout. Subjects will not be replaced if discontinued.

#### Allocation/Randomization

Patients will be randomized in the ratio 1:1. Random sequences will be generated by a research associate using Microsoft Office Excel 2017, and stored by hospital nurses in sequentially numbered, sealed and opaque envelopes. Researchers will open the corresponding numbered envelope after obtaining consent from each patient.

### Blinding

In this single-blinded trial, participants and main assessors will be aware of treatment allocation but not aware of the study hypothesis. Research assistants who are responsible for assessment and statistical analysis will be blinded to participant randomization assignments. Research assistants for assessment will be blinded to the treatment allocation throughout the study. An employee who is not involved in the study will enter the data into the computer so that the statistician will be unaware of the allocation.

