#### Clinical variables

Individuals will be diagnosed by two psychiatrists according to DSM-5 diagnostic criteria. The Mini-International Neuropsychiatric Interview (MINI), a short structured diagnostic interview, will be used to confirm the diagnosis (54).

Depression symptoms will be measured by HMRD 17, which was designed by Hamilton in 1960 (55). The reliability of Chinese version of HMRD-17 is 0.88–0.99 and the validity is 0.92 (50). Some items are defined by increasing intensity, and others are defined by number of equal valued terms. According to Davis JM, the scores of HMRD 17 ≤ 7 indicate that individuals do not have depressive symptoms; the scores >7 and ≤17 indicate that individuals have minor or moderate depression; the score >24 indicate that individuals have major depression. Two trained psychiatrists will independently conduct the assessments. This is the most widely used clinical scale and contains 17 variables.

Depression symptoms will also be measured by the Self-Rating Depression Scale (SDS), which was designed in 1965 by Zung and recommended by the United States Department of Education, Health and Welfare in psychopharmacological research (56). SDS includes 20 items, of which 10 items are positive and 10 items are negative. The form will be directly filled by patients. The row score will be derived by adding up 20 items, with maximum possible score being 80. Index score is equal to the row score × 1.24, expressed as decimal. The standard score in China is 53 and the cutoff value of total row score is 41, which is similar to the results of a study in the USA (57).

Manic symptoms will be measured by the Young Manic Rating Scale (YMRS), which contains 11 items (58). YMRS was designed by Young in 1978, and is the most widely used manic scale worldwide. YRMS contained 11 items. Five choices are included in items 1–4, 7, 10, 11, ranging from scores 0–4, while the items 5, 6, 8, 9 have five choices scored in double points (score of 0, 2, 4, 6, 8). The score ranges from 0 to 40. When the total score ≥5 and ≤10, individuals have manic symptoms and when the score ≥22, individuals have severe manic symptoms. The reliability and validity of YRMS have been examined in a previous study.

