### Data collection methods

Two permanent research assistants, majoring in psychology with uniform training will perform all assessments at baseline and after eight weeks of intervention using standard procedure. Blood sampling for the analysis of biological parameters will be performed during the same visit.

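### The protocol has the main assessors both aware of and blinded to allocation, and names two different sets of HAMD-17 raters, so the primary outcome may be scored unblinded.

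*Protocol article*

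**What the plan says.** The protocol article calls the trial single-blind and describes who knows the allocation, and who rates, in three places.

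- **Blinding.** It first says that "participants and main assessors will be aware of treatment allocation but not aware of the study hypothesis". The next sentence says "Research assistants who are responsible for assessment and statistical analysis will be blinded to participant randomization assignments", and the one after that "Research assistants for assessment will be blinded to the treatment allocation throughout the study". The term 'main assessors' is not defined anywhere.
- **Clinical variables, HAMD-17 paragraph** (where the scale is spelled HMRD 17). "Two trained psychiatrists will independently conduct the assessments". Nothing is said about whether these psychiatrists know the allocation.
- **Data collection methods.** "Two permanent research assistants, majoring in psychology with uniform training will perform all assessments at baseline and after eight weeks of intervention".

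The endpoint affected is the primary one: "The primary outcome of this study is the HAMD 17 score mean change from baseline to week 8" (Outcomes). The HAMD-17 is scored by a rater. The other depression scale, the SDS, is not: "The form will be directly filled by patients".

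**The concern.** Participants know whether they were given the exercise programme, and the control arm receives usual care with no sham activity. At the moment a HAMD-17 score is assigned, the only protection available is a rater who does not know the arm. The protocol both asserts that protection and contradicts it, and it leaves open which staff do the rating.

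Keeping allocation-aware staff unaware of the hypothesis gives little assurance. A rater who knows that a patient had an added exercise programme can form an expectation without being told what the trial is testing.

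If such a rater scores the HAMD-17, any systematic leaning is added directly to the between-group difference. It cannot be separated from the treatment effect afterwards, whether by covariance adjustment, by imputation or by blinding the analyst.

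**Working it through.** **Step 1: test each reading of 'main assessors' against the three sections.**

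| Who the main assessors are | Blinding section | HAMD-17 paragraph and Data collection methods |
|---|---|---|
| The research assistants | Contradicts itself: aware in one sentence, blinded in the next two | Still name different raters |
| The two psychiatrists | Consistent | The HAMD-17 paragraph then has allocation-aware raters score the primary outcome; Data collection methods gives the same task to the blinded assistants |
| Other staff (coach, treating clinicians) | Consistent, but the text does not say so | Still name different raters |

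A further possibility is that the psychiatrists rate only at screening. The text does not support it: their sentence stands in the description of HAMD-17 scoring, and diagnosis by two psychiatrists is covered separately at the start of Clinical variables. No reading makes all three sections agree.

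**Step 2: reproduce the planning figures used for scale.** Inputs from Sample size: difference 4.3, SD 6, α = 0.05. Two assumptions are needed: the printed power of 0.09 is read as 0.90, and the test is taken as two-sided.

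- Normal approximation: n = 2 × (1.960 + 1.282)² × 6² / 4.3² ≈ 40.9, so 41 per arm.
- Two-sample t-test (noncentral t): power 0.894 at 41 per arm and 0.901 at 42. This gives the protocol's 42.
- 20% dropout: 42 / 0.80 = 52.5, so 53 per arm, as stated.

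**Step 3: illustrate what a rater shift would do.** The size of any rater bias is not in the documents. Shifts *b* of 0.5 to 2 HAMD-17 points are assumed, with no true treatment effect, 42 per arm and SD 6.

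- Standard error of the difference: 6 × √(2/42) = 1.309.
- Noncentrality: b / 1.309. Degrees of freedom: 82. Critical value: 1.989.
- Rejection probability: P(|T| > 1.989), where T is noncentral t.

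| Assumed shift (points) | Noncentrality | Two-sided rejection rate |
|---|---|---|
| 0 | 0 | 0.050 |
| 0.5 | 0.382 | 0.066 |
| 1 | 0.764 | 0.117 |
| 1.5 | 1.146 | 0.205 |
| 2 | 1.528 | 0.327 |

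The number analysed makes only a modest difference: for a 1-point shift the rate is 0.111 at 38 per arm and 0.136 at 53. One point is 1 / 4.3 = 23% of the planned effect.

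**The case against.** The text leans towards blinded rating. The Blinding section says twice that the assessing research assistants are blinded, and Data collection methods gives them all assessments at baseline and after eight weeks, the two time points of the primary outcome. Against this stand one undefined term and one sentence about psychiatrists, who are never called unblinded. The statistician is also blinded, with data entered by an uninvolved employee. The bias sizes are assumed, and CRP, TNF-α and IL-6 are laboratory measurements that a rater cannot influence. On this view the fault is inconsistent drafting, not a decision to rate unblinded.

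Much of this is fair. Unblinded rating of the HAMD-17 is possible, not established, and the false-positive rates show sensitivity, not the bias to be expected here. Rater blinding is also not the only blinding described, though it is the only one acting when the score is made.

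The contradiction itself remains. The protocol states positively that some assessors know the allocation and names two sets of raters for the primary outcome. That is not detail which a condensed article leaves to a fuller document, and a site following the text literally could let allocation-aware staff score the HAMD-17.

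**Conclusion.** The concern holds. The protocol does not settle who rates the HAMD-17 or whether that person is blinded, and this has to be corrected because no analysis can undo biased scoring once the data are collected. The finding rests on the text alone and needs no figure.

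The scale of the risk is illustrative. It assumes SD 6, 42 analysed per arm, a two-sided 5% t-test and a rater shift that the documents do not supply. Under those assumptions a 1-point shift with no true effect gives a false-positive rate of about 12%, 1.5 points about 20%, and 2 points about 33%.

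**What to change.** - In Blinding, state that the HAMD-17 and YMRS are scored at every post-baseline visit only by the two research assistants already described as blinded, and that anyone aware of allocation, including the coach, does not score outcomes.
- Take the main assessors out of the allocation-aware group. If the term describes real staff who do know the allocation, name them and say that they do not rate.
- Align the HAMD-17 paragraph of Clinical variables with Data collection methods, so that both name the same raters. If psychiatrists are to rate, their blinding must be stated in the same terms; that would also remove the conflict.
- Extend Data collection methods to week 4 and month 4. The schedule in Table 1 has the HAMD-17 and YMRS at both visits, but the assistants are committed only to baseline and after eight weeks.
- Ask participants not to disclose their arm to the rater. As a useful but optional addition, record each rater's guess of allocation at week 8.

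The cost is protocol wording and role assignment. The blinded assistants are already in the plan, so no new role is needed, though their time at week 4 and month 4 should be confirmed.
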